### 4.3 Group Allocation

Dose cohorts will be enrolled consecutively. In **Part I** of the study, within Cohort 1 all participants will receive the 10 µg dose of *Na*-GST-1/Alhydrogel®; within Cohort 2, all will receive 10 µg of *Na*-GST-1/Alhydrogel®/GLA-AF, and so on. In **Part II** of the study, within Cohorts 7, 9 and 11 of 10 participants, 8 will be randomly assigned to receive *Na*-GST-1/Alhydrogel® and 2 to receive Butang® (see **Section 7.3**). Within Cohort 7, Cohort 9, and Cohort 11, those randomized to receive *Na*-GST-1/Alhydrogel® will receive a dose containing 10 µg, 30 µg and 100 µg of *Na*-GST-1, respectively. Also in Part II of the study, within Cohorts 8, 10, and 12 of 12 participants, 2 will be randomly assigned to receive *Na*-GST-1/Alhydrogel® and 10 to receive *Na*-GST-1/Alhydrogel®/GLA-AF. Within Cohorts 8, Cohort 10, and Cohort 12, participants will receive a dose containing 10 µg, 30 µg and 100 µg of *Na*-GST-1, respectively.

In both **Part I** and **Part II** of the study, 1 or 2 additional eligible volunteers above the number to be enrolled in a given cohort may be scheduled for a Day 0 visit, if possible. On the day of first vaccination, the first volunteers who arrive at the study clinic will be evaluated for continued eligibility and vaccinated in the order that they arrive; the additional eligible volunteers will be kept as alternates if some of the first arrivals cannot be vaccinated on the day of first vaccination (i.e., due to pregnancy, withdrawal of consent, etc.). If the alternates are not vaccinated, they will be invited to participate as members of the next dose cohort. Those alternates for the final cohorts in both Part I and Part II who are not vaccinated and therefore not enrolled in the study, will be offered vaccination with a non-study, licensed vaccine such as the tetanus toxoid or influenza vaccine.

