Dose cohorts will be enrolled and vaccinated in a consecutive fashion as described in **Section 4.3**. In **Part I** of the study, 36 volunteers will be enrolled into one of six cohorts (see **Table 3**): in the first cohort, 6 individuals will receive the 10 µg dose of *Na*-GST-1/Alhydrogel®; in the second cohort, 6 individuals will receive the 10 µg dose of *Na*-GST-1/GLA-AF; in the third and fourth cohorts, 6 volunteers each will receive 30 µg *Na*-GST-1/Alhydrogel® and *Na*-GST-1/Alhydrogel®/GLA-AF, respectively; while in the fifth and sixth cohorts, 6 volunteers each will receive 100 µg *Na*-GST-1/Alhydrogel® and *Na*-GST-1/Alhydrogel®/GLA-AF, respectively. Enrollment of these cohorts will be staggered by (at least) one-week intervals: Cohorts 2 and 3 will be enrolled and begin vaccinations at least 1 week after Cohort 1, Cohorts 4 and 5 will be vaccinated at least 1 week after Cohorts 2 and 3, and Cohort 6 will be vaccinated at least 1 week after Cohorts 4 and 5.

In **Part II** of the study, 66 volunteers will be progressively enrolled into one of six dose cohorts. In the seventh, ninth and eleventh cohorts, volunteers will be randomized to receive either *Na*-GST-1/Alhydrogel® (n=8) or Butang® (n=2), while in the eighth, tenth and twelfth cohorts, volunteers will be randomized to receive either *Na*-GST-1/Alhydrogel® (n=2) or *Na*-GST-

1/Alhydrogel®/GLA-AF (n=10). Volunteers randomized to receive *Na*-GST-1 will receive either the 10 µg, 30 µg or 100 µg dose, as outlined in **Table 3**.

As with other aluminum hydroxide-adsorbed vaccines, hypersensitivity reactions would be expected to occur within the first 24 hours after receipt of either of the two vaccines, and other severe local or systemic reactions within 72 hours of vaccination. Participants will therefore be observed for immediate reactions following each vaccination for at least 2 hours, and will have a clinical assessment either in their home or at the study clinic on Days 1, 3, 7, and 14 following each vaccination. See **Tables 2** and **3** for tabular descriptions of the vaccination schedule for all dose cohorts, as well as **Section 7.6** and **Appendix B** for a detailed description of the scheduled clinical and laboratory evaluations.

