| 20                                         |                                                                                                                                               |                                                                                                                                                                                                          |                                                                                                                                                | Vaccination 3
(Day 112)                                                                                                                                                                                  | Vaccination 3
(Day 112)                                                                                                                       |                                                                                                                                                                                                               |
| 21                                         |                                                                                                                                               |                                                                                                                                                                                                          |                                                                                                                                                |                                                                                                                                                                                                             |                                                                                                                                                  | Vaccination 3
(Day 112)                                                                                                                                                                                    |

Approximate (see **Section 7.6** for more detail). Weeks between enrollment of successive cohorts are the minimum required.

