### **7.3 Randomization Process for Part II of the Study**

For Part II of the study, the eligible volunteers assigned to Cohorts 7 to 12 will be asked to come to the study clinic on their scheduled day of enrollment into the study; transportation to the clinic will be provided. After undergoing a clinical interview and exam to ensure that they remain eligible for participation in the study, that they have had blood collected for the studies outlined in **Section 7.6**, and that females have had a urine pregnancy test performed that is documented to be negative, volunteers will be assigned a unique study number and vaccinated as described in **Section 7.5**.

Randomization to either *Na*-GST-1/Alhydrogel®, *Na*-GST-1/Alhydrogel®/GLA-AF or Butang® will be done through use of a randomization code furnished to the study vaccine manager by the data-management center. The study numbers will be assigned in the order in which the participants are enrolled in the study, so that among the first 10 study numbers in Part II of the study, 8 will be assigned to *Na*-GST-1/Alhydrogel and 2 to Butang®. Assignment of the study numbers will be done on the day of first vaccination, in the order that the study participants present for immunization.

Access to the randomization list will be exclusively limited to the study vaccine manager and their assistant. Between vaccination days, the randomization list will be stored in a sealed envelope in a locked cabinet. The study vaccine manager (and assistant) will be unblinded, but will not be involved in study participants' further evaluation.

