#### Study Day 0 (Day of First Vaccination)

1. Verify that Informed Consent was obtained.
2. Verify that all applicable eligibility criteria have been met.

3. Perform abbreviated history (including concomitant medications) and physical exam, focusing on any acute complaints.
4. Obtain blood for hematology, biochemistry, anti-GST-1 and total IgE antibody ELISAs and cellular immunology assays.
5. For females, obtain a urine sample for hCG testing. Ensure that test is negative before proceeding; a positive test will exclude the volunteer from the trial.
6. Record vital signs (blood pressure, oral temperature, and heart rate).
7. Administer the vaccine.
8. Observe for at least 2 hours after vaccination to evaluate for immediate adverse reactions. During the 2-hour post-immunization wait period, study staff will discuss signs and symptoms of potential AEs.

#### Study Day 1

1. Perform basic history and physical exam (including injection site), emphasizing examination of any acute complaints.
2. Record vital signs.

#### Study Day 3 +/- 1

1. Perform basic history and physical exam (including injection site), emphasizing examination of any acute complaints.
2. Record vital signs.

#### Study Day 7 +/- 1

1. Perform basic history and physical exam (including injection site), emphasizing examination of any acute complaints.
2. Record vital signs.

#### Study Day 14 +/- 2

1. Perform basic history and physical exam (including injection site), emphasizing examination of any acute complaints.
2. Record vital signs.
3. Obtain blood for hematology, biochemistry, anti-GST-1 and total IgE antibody ELISAs, and cellular assays.

#### Study Day 28 +/- 4

1. Perform basic history and physical exam (including injection site), emphasizing examination of any acute complaints.
2. Record vital signs.
3. Obtain blood for anti-GST-1 and total IgE antibody ELISAs and cellular assays.

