### **8.5 Criteria for Suspension of Further Injections**

If a dose of vaccine is considered significantly reactogenic (see below), dose escalation and/or additional vaccinations will be suspended until reviewed by the Medical Monitor, SMC and study sponsor (SVI). Any recommendation of the Medical Monitor and SMC to resume or suspend further injections (either for an individual participant, an entire dose cohort, or all dose cohorts) will be communicated in writing to the sponsor and Principal Investigator. All communications from the SMC will subsequently be forwarded by the investigators to the CPqRR and GWUMC IRBs.

The following criteria will be used to define significant reactogenicity (note that in Part II of the study, these apply to both the *Na*-GST-1 vaccines and Butang® vaccine, as these criteria will be applied in advance of any consideration of unblinding):

- a. One or more participants experience an SAE (as defined in **Section 8.1.2** in this protocol) that is determined to be possibly, probably, or definitely related to the vaccine (as defined in **Section 8.2.3** in this protocol), **OR**
- b. One or more participants experience a hypersensitivity reaction (a Grade 3 allergic reaction, as defined in **Appendix D**) that is possibly, probably or definitely related to the vaccine, **OR**
- c. One or more participants in a single dose cohort experience an objective physical finding or laboratory abnormality of Grade 3 or higher (with the exception of isolated Grade 3 erythema or swelling), as defined in **Section 8.2.2** in this protocol, that is determined to be probably or definitely related to the vaccine. **OR**

- d. Two or more participants in a single dose cohort experience a Grade 2 or higher safety laboratory abnormality or Grade 3 clinical AE that is possibly, probably or definitely related to the vaccine.

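### No interval is required between first doses within Cohorts 1 and 2, so all six participants in each first-in-human cohort can be dosed before a delayed reaction appears

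*Protocol*

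**What the plan says.** Section 4.3 covers both parts of the study. It allows one or two spare volunteers to be scheduled for Day 0 and then says that "the first volunteers who arrive at the study clinic will be evaluated for continued eligibility and vaccinated in the order that they arrive". Spare volunteers who are not used that day are invited into the next cohort. Table 2 gives each Part I cohort a single calendar week for its first vaccination.

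The spacing rules concern successive cohorts. For Part I, section 4.1 says: "Enrollment of these cohorts will be staggered by (at least) one-week intervals". The note under Table 3, which also stands under Table 2, reads: "Weeks between enrollment of successive cohorts are the minimum required".

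On timing of reactions, section 4.1 states that "hypersensitivity reactions would be expected to occur within the first 24 hours after receipt of either of the two vaccines". For the remaining severe reactions it gives a window of 72 hours. Section 7.6 asks staff on Day 0 to "Observe for at least 2 hours after vaccination to evaluate for immediate adverse reactions". That applies to each participant separately and is not a condition for injecting the next one.

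Sections 1.9 and 1.11 state that neither Na-GST-1 nor GLA-AF has been given to humans. Section 8.5 suspends further vaccination after a single vaccine-related SAE or a single related Grade 3 allergic reaction, among other triggers.

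**The concern.** The protocol expects the reactions of most interest within 24 hours, or within 72 hours for other severe reactions. It uses a gap of at least one week to protect the next cohort. Nothing comparable protects members of the same cohort. If the six in Cohort 1, or the six in Cohort 2, are dosed in one session, a reaction that begins that evening or overnight is seen only after all six have been exposed. The suspension rule then protects later doses and later cohorts, but not the remaining first doses of that cohort. These two cohorts are where least is known in humans about the antigen and the adjuvant.

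**Working it through.** **Counts.** Part I has 6 × 6 = 36 participants and Part II has 3 × 10 + 3 × 12 = 66, total 102, as the protocol states. After Cohort 1 has its first dose, 102 − 6 = 96 first doses can still be withheld. Later cohorts are therefore protected, and the exposed group is the rest of the same cohort.

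**Timing.** A single day's session is shorter than 24 hours. When the last of six is injected, even the first arrival has not passed the expected window for hypersensitivity, and the Day 1 assessment has not taken place.

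**Size of the gain.** The documents give no reaction rate for Na-GST-1 or GLA-AF, so the rate is an assumption. Let p be the probability that an active first dose causes a reaction that starts after the session, is found by the 24-hour check and leads to a hold. Participants are taken as independent, and dosing is taken as not resumed after a hold. All 6 in each cohort receive active vaccine. With two dosed first and four waiting:

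- chance of a hold per cohort = 1 − (1 − p)²
- expected reactors averted per cohort = [1 − (1 − p)²] × 4p
- expected reactors without a lead-in, both cohorts = 12p

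| p | Hold, per cohort | Averted, per cohort | Averted, both cohorts | Reactors without lead-in, both cohorts |
|---|---|---|---|---|
| 1% | 0.0199 | 0.0199 × 0.04 = 0.0008 | 0.0016 | 0.12 |
| 5% | 0.0975 | 0.0975 × 0.20 = 0.0195 | 0.039 | 0.60 |
| 10% | 0.19 | 0.19 × 0.40 = 0.076 | 0.152 | 1.20 |

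The chance that two or more of six react falls from 3.3% to 1.5% at p = 5%, and from 11.4% to 5.2% at p = 10%. At p = 1% it is 0.1% either way.

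**These are upper bounds.** Suppose p is instead the rate of all reactions and only half start after the session. The hold probability then uses p/2. At 10% it is 1 − 0.95² = 0.0975, and the number averted across both cohorts is 2 × 0.0975 × 0.40 = 0.078. At 5% it is 2 × 0.049375 × 0.20 = 0.020.

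**Whether a hold would be called.** Appendix D lists urticaria under Grade 2 hypersensitivity, and Table 4 grades urticaria treated orally or topically as Grade 2. Trigger b in section 8.5 starts at Grade 3, and the clinical parts of triggers c and d also need Grade 3. Non-serious Grade 2 urticaria in a lead-in participant would meet none of them, so a lead-in that relied on section 8.5 alone could miss this signal.

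**The case against.** The protocol makes no false statement here. Section 4.3 deals with arrival order and spare volunteers, and a site could spread a cohort over several days without breaching it. That stands: one-day dosing is implied, not required, and the point is an added safeguard.

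The prior evidence is also reassuring. The rat study showed no safety signal (section 1.6). None of the 179 samples tested by ImmunoCAP exceeded the IgE cut-off (section 1.4). GLA-SE was tolerated in humans at doses up to 2.5 µg (section 1.11). Dosing starts at 10 µg. Section 1.10 gives urticaria in 0.1% of hepatitis B vaccine recipients, and local reactions of any severity in 7.6% to 16.7% for aluminum hydroxide-adsorbed vaccines. Against those figures, 10% for hold-triggering reactions looks high. At 0.1% the formula gives about 0.00002 reactors averted. All of this shrinks the gain without removing it, since neither new product has a human rate.

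A reader might infer more than the documents support:

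- *Any reaction comes too late for the cohort.* Section 8.5 suspends additional vaccinations, so a reaction during the session may spare late arrivals. The point covers only reactions that start after the session.
- *Section 7.3 proves one-day dosing.* It says "Assignment of the study numbers will be done on the day of first vaccination, in the order that the study participants present for immunization", but it is headed and worded for Part II and is no evidence for Cohorts 1 and 2.
- *Cohort 7 is equally exposed.* It starts only after SMC review of Cohort 6 through Day 70, and volunteers with IgE to the antigen above 0.35 kUA/L are excluded. With 8 active and 2 Butang recipients, a two-person lead-in would contain at most one active recipient with probability (32 + 2)/90 = 38%. A lead-in there is optional.
- *The 3 of 7 urticaria cases with Na-ASP-2 give a rate.* Those were previously infected adults with raised IgE to a different antigen, and onset was at 1 to 2 hours, which may fall inside the session.

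**Conclusion.** The point holds for Cohorts 1 and 2 and is a low-priority improvement worth considering. As written, all six first-ever recipients of Na-GST-1, and all six of GLA-AF, can be dosed before the protocol's own 24-hour window has passed for any of them. A delayed reaction would then stop only later doses and later cohorts. At assumed hold-triggering rates of 1%, 5% and 10%, at most 0.002, 0.04 and 0.15 reactors are averted across the two cohorts. These bounds assume that every reaction starts after the session and before the 24-hour check, leads to a hold, and that dosing does not resume, whereas section 8.5 suspends only pending review. The case rests on the low cost of a conventional first-in-human precaution, not on a large expected benefit.

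**What to change.** Amend section 4.3 for first doses in Cohorts 1 and 2 only:

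1. Vaccinate two participants and wait at least 24 hours.
2. Check their existing Day 1 assessment against section 8.5.
3. Have the Medical Monitor review any hypersensitivity of Grade 2 or higher. Section 8.10 already lets the Monitor put the study on hold.
4. If there is no hold, dose the remaining four.

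Part I is open-label and not randomized, so allocation and blinding are unaffected.

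The cost is a protocol amendment and one extra dosing day per cohort, which at the minimum schedule moves later cohorts by at most 2 days in Part I of a 24-month trial. Spare volunteers return on the second day. Cohort 2 needs a fresh GLA-AF mix, because the mixture must be used within 24 hours, and possibly a new vial, because the multi-dose vials have no preservative. A 24-hour hold leaves part of the 72-hour window for other severe reactions uncovered.

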### 4.4 Blinding

**Part I** of the study will be an open label phase 1 trial. In **Part II**, investigators and participants will be blinded as to an individual study participant's allocation to either *Na*-GST-1/Alhydrogel®, *Na*-GST-1/GLA-AF or Butang® vaccine until all participants have completed their Day 140 visit, the safety and primary immunogenicity data have been monitored and entered into the database, and the database has been locked. Only the study vaccine manager (and potentially an assistant) will be aware of the participants' vaccine allocation. The study vaccine manager will refer to the unique randomization code assigned to that participant to determine the assigned vaccine for each participant (see **Section 7.3**). Vaccine will be prepared by the study vaccine manager in a separate room and the vaccine-filled syringes will be handed to the vaccinator(s). Since the 10 and 30 µg doses of the *Na*-GST-1 formulations are of different volumes (0.1 ml and 0.3 ml, respectively) than that of Butang® (1.0 ml), the contents of all syringes will be disguised using opaque tape. As a further precaution, the vaccinator(s) will not be based in Americaninhas and will not be involved in assessments of reactogenicity or adverse events.

Due to the staggered, dose-escalation design of Part II of the trial, it will not be possible to blind to the dose of *Na*-GST-1 that an individual may have received. That is, those participants

assigned to Cohort 7 may receive either the 10 µg dose of *Na*-GST-1/Alhydrogel or the Butang® vaccine, whereas Cohort 8 will receive either 10 µg *Na*-GST-1/Alhydrogel or *Na*-GST-1/GLA-AF, Cohort 9 will receive either 30 µg *Na*-GST-1/Alhydrogel or Butang®, and Cohort 10 will receive either 30 µg *Na*-GST-1/Alhydrogel or *Na*-GST-1/GLA-AF, and so on. Since Cohorts 9 and 10 will receive their vaccinations after Cohorts 7 and 8 (see **Table 3**) and Cohorts 11 and 12 will receive their vaccinations after Cohorts 9 and 10, it will not be possible to blind to the dose of *Na*-GST-1 that may have been given, only to the allocation between *Na*-GST-1/Alhydrogel, *Na*-GST-1/GLA-AF, or Butang®.

The investigators will be unblinded to participants' vaccine allocation status after all have had their study Day 140 visit (see **Section 8.10**). After this point, the study will be single-blinded (i.e., study participants will remain blinded to what vaccine they have received). The principal justification for unblinding the investigators before the final study visit has been completed is that the safety and immunogenicity data acquired during the vaccination phase of the study will be crucial in guiding the clinical development plan for *Na*-GST-1, and we feel that, to make an informed decision as to whether or not to proceed to pediatric trials, we must first assess the unblinded data in a timely fashion.

